**Inclusion criteria**
Adults aged 19 years or olderFulfillment of the diagnostic criteria for substance use disorder according to the *Diagnostic and Statistical Manual of Mental Disorders, Fifth Edition* [26] and diagnosis under the *International Classification of Diseases, Tenth Revision*, F11, F12, F14, F15, or F19 categories [27]At screening, completion of the Drug Abuse Screening Test–Korean Version [28]Having initiated psychiatric treatment within 30 days prior to screening and intention to continue treatment for at least 3 monthsSelf-reported history of drug use within 30 days prior to screening (or within 60 days if recently discharged from a controlled environment)Ability to read and write Korean without difficultyAbility to use a smartphone and mobile app without difficultyVoluntary provision of written informed consent after receiving sufficient explanation of the studyNo history of dementiaFor women of childbearing age, agreement to use medically acceptable contraception during the study periodIn special cases, legally authorized representatives may consent on behalf of participants; such participants are also eligible
**Exclusion criteria**
Presence of any advanced, progressive, or unstable disease that could endanger the patientNeurological disorders that may cause cognitive impairmentNeurodegenerative diseases other than depression or severe psychiatric symptoms that would preclude study participationCurrent uncontrolled seizure disorderHistory of brain injury with loss of consciousness lasting more than 1 hour or hospitalization due to traumatic brain injury within the past 3 yearsHearing or visual impairment that would interfere with completion of study requirementsLack of a smartphone capable of installing the investigational medical appPregnant or breastfeeding womenConcurrent participation in another clinical trial or participation in another trial within 30 days prior to screeningDetermination by the investigator to be otherwise unsuitable for the trial

**Table 1. T1:** SPIRIT (Standard Protocol Items: Recommendations for Interventional Trials) checklist: clinical trial–related items.

	Clinical trial period						
	Enrollment—visit 1 (week –4)	Assignment—visit 2 (week 0; baseline)	After assignment				Completion—visit 7 (week 12)
			Visit 3 (week 4)	Visit 4 (week 6)	Visit 5 (week 8)	Visit 6 (week 10)	
Enrollment							
Informed consent	✓						
Screening	✓						
Eligibility check (inclusion and exclusion criteria)	✓						
Demographics and social history	✓						
Physical examination	✓						
Prior medication history	✓						
Pregnancy test	✓	✓	✓^a^	✓^a^	✓^a^	✓^a^	✓^a^
Urine drug test		✓	✓	✓	✓	✓	✓
Randomization		✓					
Intervention							
Investigational DTx^b^		✓	✓	✓	✓	✓	✓
TAU^c^	✓	✓	✓	✓	✓	✓	✓
Assessment							
Abstinence record sheet and mobile record verification							✓
Questionnaire assessment^d^		✓			✓		✓
Compliance and retention assessment		✓	✓	✓	✓	✓	✓
Adverse event monitoring		✓	✓	✓	✓	✓	✓

a Proceed, if applicable.

b DTx: digital therapeutics.

c TAU: treatment as usual.

d Questionnaire assessment: University of Rhode Island Change Assessment Scale–Drug Offender, Hospital Anxiety and Depression Scale, Cognitive Reappraisal Questionnaire, and Behavioral Activation for Depression Scale.

### Outcome Measures

#### Primary Outcome Measure: Abstinence Success Rate During the Previous 4 Weeks

The primary end point is the abstinence success rate during the final 4 weeks (weeks 9‐12) of the 12-week trial. Abstinence success is defined as meeting both of the following criteria: (1) testing negative on urine drug screens conducted at study visits and (2) reporting “no drug use” on the abstinence check function within D-STOP, consistently maintained throughout the final 4-week period. Participants who satisfy both conditions are classified as achieving abstinence success. The designation of abstinence during the final 4 weeks (weeks 9‐12) of the 12-week trial as the primary efficacy end point was informed by the primary efficacy end point used in the clinical trial of RESET-O.

For the control group, D-STOP is not provided. Instead, abstinence status will be monitored using a paper-based checklist to record participants’ self-reported drug use.

#### Secondary Outcome Measures

##### Abstinence Success Rate During the 12-Week Treatment Period

The proportion of participants achieving abstinence at any point during the 12-week study period will be collected. These data will inform evaluation of abstinence duration and maintenance.

##### Treatment Retention Rate During the 12-Week Treatment Period

The proportion of participants who complete the 12-week study without dropout will be assessed. Treatment retention is defined as the completion of all trial procedures without premature discontinuation. This measure is particularly important for patients with SUD, who face high relapse rates. High treatment retention itself can serve as an indicator of the feasibility and validity of the D-STOP app.

### Data Collected Within D-STOP

The following variables will be collected: (1) longest abstinence period, (2) total abstinent days, and (3) results from the following psychometric instruments.

#### University of Rhode Island Change Assessment Scale–Drug Offender (Korean Version; Drug-Related Readiness to Change Questionnaire)

Originally developed by McConnaughy et al [29] and validated in Korean by Chung et al [30], the University of Rhode Island Change Assessment Scale–Drug Offender is a 24-item questionnaire scored on a 5-point Likert scale. It comprises 3 stages (precontemplation, contemplation, and action or maintenance). Scores of 7 or lower indicate precontemplation, scores of 8 to 11 indicate contemplation, and scores of 12 or higher indicate action or maintenance. Reliability (Cronbach α) has been reported as 0.83 overall, 0.82 for precontemplation, 0.79 for contemplation, and 0.81 for action or maintenance. Construct and convergent validity indexes exceed 0.5 and 0.7, respectively, confirming strong reliability and validity.

#### Hospital Anxiety and Depression Scale (Korean Version)

On the basis of the Hospital Anxiety and Depression Scale by Zigmond and Snaith [31], the Korean version was validated by Oh et al [32]. The 14-item instrument, rated on a Likert scale from 0 to 3, consists of 7 anxiety items and 7 depression items. Cutoff scores are 7 or lower for healthy, 8 to 10 for borderline anxiety or depression, and 11 or higher for clinical anxiety or depression.

#### Cognitive Reappraisal Questionnaire

Developed by Kim [33] in South Korea, the Cognitive Reappraisal Questionnaire assesses 2 subtypes of cognitive reappraisal (objectifying and positive reappraisal). It is a validated 20-item questionnaire rated on a Likert scale from 1 to 7. The measure evaluates the frequency of specific emotion regulation strategies. Internal consistency (Cronbach α) was reported as above 0.80 for both subscales, indicating excellent reliability.

#### Behavioral Activation for Depression Scale

The Behavioral Activation for Depression Scale is a 25-item self-report questionnaire designed to assess patient activation levels and treatment response based on behavioral activation theory. It consists of 4 subscales: activation, avoidance or rumination, work or school impairment, and social impairment, each rated on a Likert scale from 1 to 7. The Korean version was validated by Oh et al [34]. Overall internal consistency of a Cronbach α value of 0.91 has been reported, with subscale Cronbach α values ranging from 0.76 to 0.90, demonstrating excellent reliability.

### Psychiatric and Psychological Intervention: CBT-Based DTx for SUD (D-STOP)

#### Overview

The DTx app used in this study was developed based on CBT. In addition, to enable patients to process information at their own pace and attempt treatment in alignment with their recovery plans, the app incorporates visual materials. These are grounded in established psychiatric and psychological approaches, including MET, psychoeducation, mindfulness, and conditioned reflex inhibition techniques, thereby providing a comprehensive therapeutic intervention.

#### Procedures

This clinical trial is currently in the recruitment phase. Recruitment strategies include conducting screening tests for patients with SUD who present at 1 of the 4 participating regional medical institutions. Eligibility will be determined based on the inclusion and exclusion criteria described above, and suitable participants will be enrolled. Additional recruitment will be carried out through community organizations (eg, the Seoul branch of the Korea Association Against Drug Abuse) using external advertisements.

During the 12-week trial period, participants will be required to attend 7 visits. At each visit, the following will be assessed: (1) abstinence status within the app, (2) treatment adherence, (3) diagnostic assessments for secondary end points, and (4) urine drug screens and pregnancy tests.

If drug relapse is detected through urine testing or through abstinence status recorded on the app during weeks 1 to 8, the participant will continue in the clinical trial. However, relapse occurring during weeks 9 to 12, which correspond to the assessment period for the primary end point, will be considered treatment failure.

With respect to treatment adherence, if participants use less than 35% of the app’s therapeutic services, the study psychiatrist or clinical research coordinator will encourage them to improve their engagement.

Upon enrollment, participants will be provided with the DTx app. Over the course of the 12-week self-management program, they will complete 17 modules accessible via the app: 6 treatment modules, 4 emergency modules, 1 daily life management module (via a calendar), and 6 relaxation training modules.

Throughout the trial, adverse events will be monitored. If an adverse event occurs, it will be documented in the adverse event log and reported to the study sponsor within 24 hours via the rapid adverse event reporting system.

#### D-STOP Intervention Process and Treatment Mechanism

D-STOP consists of 17 modules; however, each module is not limited to a single therapeutic method. Rather, an embedded algorithm dynamically provides different therapeutic components depending on participants’ responses. For example, the treatment case module includes 30 video-based materials organized into 5 thematic categories, with 6 videos assigned to each category. Other treatment modules also contain multiple therapeutic materials, and the total number of therapeutic components in the entire program, including treatment case materials, is 79.

Unlike RESET-O, this study places greater emphasis on the delivery of individual therapeutic materials rather than the number of modules completed. This design was adopted to address potential screen fatigue associated with prolonged use of app-based treatment. Accordingly, D-STOP was developed not merely as an educational program but also as an interactive therapeutic system. The visual materials presented to patients typically last approximately 1 to 2 minutes, and the program promotes multisensory engagement through tactile interaction via manual input, auditory learning through listening exercises, and vocal practice through spoken responses. This multisensory approach is intended to facilitate active participation and experiential learning.

On average, completing a single therapeutic activity requires approximately 10 minutes. Through the recommendation system embedded within the app, participants are generally encouraged to complete approximately 3 therapeutic activities per day. In addition, an acuity assessment conducted every 2 weeks identifies participants’ current clinical needs and dynamically recommends appropriate therapeutic components. Through this process, D-STOP provides a personalized treatment pathway tailored to each participant’s clinical condition. Participants are expected to engage with the intervention regularly throughout the 12-week treatment period.

#### D-STOP Modules

##### Overview

The modules implemented in D-STOP were not designed to simply replicate conventional psychotherapeutic approaches. Instead, they were developed with a strong emphasis on user interface and user experience to maximize patient engagement with the app while maintaining the therapeutic efficacy of established psychological interventions (Table 2 and Figure 1).

**Table 2. T2:** D-STOP module list.

Category	Module
CBT^a^	Module 1: drug use tracking practice Module 2: emotional recognition and management Module 3: stress recognition and management Module 4: external factor recognition and management
MET^b^	Module 5: treatment case Module 6: goal cards Module 7: treatment fidelity Module 8: coping activity log
Mindfulness	Module 9: cyclical sigh breathing Module 10: the 5-4-3-2-1 grounding technique Module 11: progressive muscle relaxation Module 12: urge surfing Module 13: 5-sense mindfulness practice Module 14: silent mindful walking
CM^c^	Module 15: calendar Module 16: daily activities Module 17: drug check

a CBT: cognitive behavioral therapy.

b MET: motivational enhancement therapy.

c CM: contingency management.

**Figure 1. F1:**
[figure not shown]
Sample screenshots of the D-STOP app: (A) main access screen; (B) home screen; (C) treatment module screen; (D) calendar screen; (E) emergency coping screen; and (F) schedule setting screen.

##### CBT Module

The CBT module was designed differently from traditional CBT formats. Instead of focusing primarily on identifying negative thoughts (automatic thoughts) and gradually inducing behavior change through multiple sessions, the module aims to help patients quickly recognize their problems and adjust both cognition and behavior through small, daily behavioral modifications.

In the drug use tracking practice module, patients are encouraged to recall and reflect on their previous experiences of drug use. This process helps patients identify the underlying factors that contributed to their substance use within the D-STOP intervention. While completing this exercise, patients are asked to report the primary reason associated with their drug use experience. On the basis of the identified factor, the system recommends and initiates 1 of 3 follow-up modules—emotional recognition and management, stress recognition and management, or external factor recognition and management—to facilitate a more detailed exploration of the relevant triggers.

##### MET Module

Traditional MET includes a variety of approaches. However, in D-STOP, the MET module was designed not as a therapist-led counseling intervention but as a self-guided module intended to help patients identify their own motivation while participating in the program, thereby strengthening their capacity to overcome addiction.

Patients are presented with treatment case scenarios involving individuals who encountered or reused drugs due to circumstances similar to the participants’ own. By observing how these individuals eventually recovered from addiction, patients may experience a mirroring effect, which can foster a belief that they too are capable of overcoming substance dependence.

To sustain this emerging motivation, the program provides a “goal card” function through which patients can define personal reasons for recovery or identify motivational triggers that reinforce their commitment to overcoming addiction. In addition, to encourage lifestyle changes, the app recommends alternative activities that can be easily scheduled within a calendar system. This approach supports contingency-based behavioral management and promotes continued engagement with recovery-oriented behaviors.

Furthermore, as patients consistently participate in the program, a visual treatment progress curve is presented within the app. The upward trajectory of this progress indicator helps patients recognize their gradual recovery from addiction and improvements in quality of life, thereby reinforcing their motivation to continue treatment.

##### Mindfulness Module

Finally, the mindfulness component was developed in a manner closely aligned with traditional mindfulness practices and implemented in a format that patients can easily observe and follow. This module introduces 6 relaxation-based techniques designed to help patients manage and reduce cravings associated with substance use.

The techniques are presented in two formats: (1) step-by-step guided exercises that can be practiced gradually and (2) rapid relaxation strategies that can be applied immediately when cravings become intense.

These practices aim to help patients regulate craving-related distress and restore psychological stability through focused attention and sensory awareness.

### Data Analysis

All data collected in this trial will be analyzed based on the entire screened population. The number of participants excluded from the safety set and the reasons for exclusion will be reported relative to all enrolled participants. Exclusions from the full analysis set will be described relative to the safety set, and exclusions from the per-protocol set will be described relative to the full analysis set. The primary efficacy analysis will be conducted on the full analysis set according to the intention-to-treat principle.

Participants who discontinue the study prematurely (dropouts) will be included in the analysis in accordance with the intention-to-treat principle. Missing outcome data will not be imputed. If missing values occur in outcomes related to abstinence status, the participant will be considered as having failed (failure) for the purpose of analysis.

For efficacy analyses, the primary end point is the abstinence success rate during the final 4 weeks of the trial. This end point is intended to evaluate the efficacy of the DTx intervention in patients with SUD. Statistical significance will be assessed using multiple logistic regression analyses adjusting for stratification factors such as stimulant vs nonstimulant drug use and baseline abstinence status (abstinent vs nonabstinent) as covariates. The treatment effect will be expressed as the adjusted odds ratio for the experimental group relative to the control group along with 2-sided 95% CIs.

Superiority of the experimental group over the control group will be concluded if both of the following criteria are satisfied: (1) the 2-sided *P* value is less than .05, and (2) the lower bound of the 2-sided 95% CI for the adjusted odds ratio exceeds 1.0.

The secondary efficacy end points include (1) abstinence maintenance rate during the 12-week treatment period, (2) treatment retention rate during the 12-week treatment period, (3) total number of abstinent days, (4) longest duration of consecutive abstinent days, and (5) results from psychiatric and psychological assessment tools.

For these outcomes, multiple logistic regression analyses and analyses of covariance will be performed to compare differences between the experimental and control groups.

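### The Data Analysis section contradicts itself on who is analysed, and its no-imputation rule with ANCOVA leaves out dropouts it says are included in the questionnaire analyses

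*Protocol article*

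**What the plan says.** Everything at issue stands in the Data Analysis section of the protocol article.

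- **Overall population:** "All data collected in this trial will be analyzed based on the entire screened population".
- **Chain of sets:** "The number of participants excluded from the safety set and the reasons for exclusion will be reported relative to all enrolled participants". Next, "Exclusions from the full analysis set will be described relative to the safety set", and the per-protocol set is taken in turn from the full analysis set.
- **Primary analysis:** "The primary efficacy analysis will be conducted on the full analysis set according to the intention-to-treat principle".
- **Dropouts:** "Participants who discontinue the study prematurely (dropouts) will be included in the analysis in accordance with the intention-to-treat principle".
- **Missing data:** "Missing outcome data will not be imputed", followed directly by "If missing values occur in outcomes related to abstinence status, the participant will be considered as having failed (failure) for the purpose of analysis".
- **Secondary outcomes, including the questionnaire scores:** "multiple logistic regression analyses and analyses of covariance will be performed to compare differences between the experimental and control groups".

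Three other places matter. Table 1 puts screening at week -4, randomisation at week 0 and the questionnaires at weeks 0, 8 and 12. The Randomized Controlled Trial section says that allocation follows completed screening. The Participants section treats a visit missed by more than 5 days as discontinuation of the study.

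**The concern.** There are three separate problems in one section.

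1. A comparison of arms needs an arm for each person. Screen failures have none, so the screened population cannot be the base for all analyses, and the sentence clashes with the intention-to-treat statement that follows it.
2. A full analysis set drawn from the safety set inherits whatever condition defines the safety set. Safety sets are often conditioned on exposure. In this open-label trial exposure differs by arm: an app can go unopened, whereas usual care is largely the continuation of existing treatment. If such a condition applied, exclusions after randomisation could differ by arm and undo the protection that intention-to-treat is meant to give.
3. Including dropouts and imputing nothing can both hold only if some rule gives dropouts an outcome or the model can use their partial data. For abstinence there is such a rule. For the questionnaires there is none, and an ANCOVA of one visit uses only people with a score at that visit. At stake are precision and, if leaving the trial after week 8 depends on the week-8 score, bias in the week-12 comparison.

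**Working it through.** **Step 1: the screened population.** Screening is at week -4 and randomisation at week 0, after eligibility is confirmed. Screen failures therefore have no arm. The sentence can be true of a participant-flow count but not of an efficacy analysis. The primary analysis is named separately, on the full analysis set. The result is a contradiction in the text; no comparison of arms on screened people is specified anywhere.

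**Step 2: the nesting.** The stated order is enrolled, then safety set, then full analysis set, then per-protocol set. It follows that the full analysis set lies inside the safety set. It does not follow that any randomised person is missing from it, because the article defines neither set. If the safety set holds everyone randomised, this step of the chain costs nothing.

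**Step 3: missing outcomes, by endpoint.**

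| Endpoint | Rule stated | Dropouts kept? |
|---|---|---|
| Primary abstinence and other abstinence-status outcomes | Missing counts as failure | Yes, within the full analysis set |
| Retention | Dropout is itself the outcome | Yes |
| Questionnaire scores | No imputation; ANCOVA | Not at a visit without a score |

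Counting missing abstinence as failure is itself a single imputation. It therefore also contradicts the sentence just before it unless it is labelled as an exception.

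**Step 4: what the week-8 scores are worth.** The article gives no dropout rate and no correlation, so these inputs are assumptions:

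- correlation between week-8 and week-12 scores, r = 0.6 to 0.8;
- 15% missing at week 8, so a fraction n8 = 0.85 observed;
- 25 to 30% missing at week 12, so n12 = 0.75 to 0.70 observed;
- anyone missing at week 8 is also missing at week 12.

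Using week-12 scores alone, the variance of the week-12 mean is proportional to 1/n12. Using week 8 as well, it is proportional to (1 - r²)/n12 + r²/n8. The ratio of the second to the first is

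(1 - r²) + r² × n12/n8.

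- r = 0.6, n12 = 0.75: 0.64 + 0.36 × 0.882 = 0.958
- r = 0.6, n12 = 0.70: 0.64 + 0.36 × 0.824 = 0.936
- r = 0.8, n12 = 0.75: 0.36 + 0.64 × 0.882 = 0.925
- r = 0.8, n12 = 0.70: 0.36 + 0.64 × 0.824 = 0.887

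The variance falls by about 4 to 11%. With 118 participants, 59 per arm, the people with a week-8 but no week-12 score would number 118 × (0.85 - 0.75) = 12 to 118 × (0.85 - 0.70) = 18. In effective numbers the gain runs from 59 × 0.75/0.958 = 46.2 against 44.3 per arm, to 59 × 0.70/0.887 = 46.6 against 41.3. That is about two to five participants per arm.

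**The case against.** The strongest reply is that the section is an accounting cascade (screened, enrolled, safety set, full analysis set, per-protocol set) and that its first sentence is a condensed statement about participant flow. A reader might infer that efficacy is to be analysed on all screened people. The text does not support that, since the primary analysis is expressly placed on the full analysis set. This part of the reply stands, and it makes the first problem one of wording.

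A reader might also infer that randomised participants who never open the app are dropped from the primary analysis and that the false-positive rate rises. As an illustration, suppose true success is 30% in both arms, or 17.7 of 59, and 3 to 12 D-STOP failures are removed. The apparent D-STOP rate becomes 17.7/56 = 31.6% to 17.7/47 = 37.7%, and the odds ratio 1.08 to 1.41 instead of 1.00. But nothing in the article ties either set to app use. The number excluded from the safety set may be zero. Table 1 labels the week -4 visit as enrolment, so every exclusion could be someone never randomised, although the Abstract uses enrolled for people who have passed screening. The Ethical Considerations section also provides an orientation session when app access is given. The illustration therefore shows one hypothetical definition and is no estimate for this trial. Only the conditional statement survives.

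On the questionnaires, it can be said that the article does not name the visit for the ANCOVA, that week 8 might have its own, and that missing-data detail for secondary scales belongs in an analysis plan that is not shown. The first two are fair. Yet a separate week-8 ANCOVA would still leave those people out of the week-12 comparison. The third does not dispose of the point, because the article goes beyond silence: it states that dropouts are included, that nothing is imputed, and that ANCOVA is a method, and these do not fit together for the scores. It is also true that a mixed model does not rescue people who leave before any score after baseline.

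**Conclusion.** The point holds in three parts of unequal weight.

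- The screened-population sentence is wrong as an analysis population and contradicts the text after it. It does not drive the primary result.
- The full analysis set is described as drawn from the safety set, which is the wrong order for an intention-to-treat claim. Whether it loses any randomised participant is not stated, so any bias is conditional and its size unknown.
- The rules for dropouts and missing data do not fit together for the questionnaires. This is the part with a practical consequence. It touches secondary endpoints only; a reader should not infer that the primary analysis discards dropouts, because missing abstinence counts as failure.

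The gain from using week 8 is modest: about 4 to 11% lower variance of the week-12 mean, on the assumed correlations and missingness above. Bias is also reduced if dropout depends on the week-8 score, provided scores are missing at random given the observed data.

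**What to change.** 1. Limit the screened population to participant-flow reporting.
2. State that the full analysis set is all randomised participants, analysed as assigned, and is independent of the safety set. Define the safety set separately.
3. Keep missing abstinence as failure, and say that it is the explicit exception to the rule of no imputation.
4. Analyse the questionnaire scores with a mixed model for repeated measures on weeks 8 and 12, with baseline score, arm, visit and the arm-by-visit interaction. Report the week-12 contrast from that model, and state how many participants have no score after baseline, since they still contribute no outcome.

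The cost is wording, slightly more analysis work and a missing-at-random assumption for the questionnaires. No new data are needed, because Table 1 already schedules the week-8 questionnaires. Data collection is expected to run to November 30, 2026, so the change can be recorded and dated before the final analysis.
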